### Expectation and Engagement

Apart from the degree of physical exercise, another issue is that improvements in cognitive functions also depend on psychological factors such as one’s expectation about the outcome (Boot et al., 2013a) or engagement during the intervention (Green et al., 2014; Benzing et al., 2016). This study is designed to address these issues by considering the expectations and engagement of the participants. At the first meeting, the study protocol is explained to participants, followed by a practice session with the Stroop task and both video games. They are told that it should be investigated whether high-intensity or low-intensity training and whether Brain Age or Tetris has a stronger effect on Stroop task and brain activity. The participants are blinded to the expected outcome and are asked after the last session of the familiarization phase and after the last session of the intervention phase about their subjective feeling to what extent the interventions might affect cognition (Boot et al., 2013a). Results of earlier studies suggest that differences of subject feelings (e.g., enjoyment, motivation, fatigue, satisfaction) between the experimental (high-intensity physical exercise, Brain Age video game) and control (low-intensity physical exercise, Tetris video game) condition might affect the improvement of cognitive function (Green and Bavelier, 2008). Because Brain Age and Tetris have been shown to have equal levels of engagement, it is expected that no significant difference exists in engagement between Brain and Tetris. In case there is a difference, it will be checked whether the performance at the Stroop task as well as the brain activity in the fMRI correlate with the engagement score. Based on the suggestion, the participants are asked to respond to questionnaires related to their subjective feelings weekly after each intervention (Boot et al., 2013a; Nouchi et al., 2013). Participants rated both questionnaires using a Likert scale, with 1 representing strong disagreement and 7 representing strong agreement with the given statements.

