### Secondary Hypotheses

Expectations for improvement in various fields might differ in some regards (e.g., performance at cognitive task, performance at everyday tasks) between the experimental and the control task (high vs. low intensity or Brain Age vs. Tetris, respectively).Expectations of participants for improvement at the cognitive task (for both, physical exercise and video game interventions) correlate with the Stroop task performance (inversely with reaction time).Engagements of participants during experimental and control conditions (high vs. low intensity or Brain Age vs. Tetris, respectively) are not significantly different from each other.

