### Sample Size

Calculation of the sample size is not possible because no similar study has been reported to date. Soares et al. (2016) report that the optimal sample size for adequate reliability and power in fMRI studies might be between 16 and 32 participants. Zysset et al. (2007), who also conducted an experiment with Stroop task in fMRI, respectively used 23 and 24 participants per group. We also aim to include 24 participants.

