### Stroop Task Analysis

We will use R (R Core Team, 2018) and lme4 (Bates et al., 2015) to perform linear mixed effects analysis of cognitive performance in dependence of physical exercise and video gaming. For reaction time at the Stroop task, we enter physical exercise intensity (high/low), video game (Brain Age/Tetris), week (1, 2, 3, 4), congruency of the Stroop task (congruent/incongruent), age (60–70 years), and gender (male/female) as fixed effects into the model. As random effects, we have intercepts for participants, as well as by-participant random slopes for the effect of physical exercise intensity and video game. Expectations for improvement at the cognitive task also enter as fixed effects into the model and the correlation with other predictors should be checked. For the correct answer count at the Stroop task, we will use the generalized linear mixed-effects model analysis and take the same fixed and random effects as above. Visual inspection of residual plots should be checked to ascertain whether they reveal any marked deviations from homoscedasticity or normality. *P*-values are obtained from likelihood ratio tests of the full model with the effect in question against the model without the effect in question.

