### Analysis of Expectation and Engagement

We use the same linear mixed-effects analysis for the Stroop task analysis. For the rating of expectation and engagement, we enter physical exercise intensity (high/low), video game (Brain Age/Tetris), week (0, 1, 2, 3, 4), age (60–70 years), and gender (male/female) as fixed effects into the model. As random effects, we have intercepts for participants, as well as by-participant random slopes for the effect of physical exercise intensity and video game. Experimental and control condition are compared whether any significant differences exist in expectation and engagement between the experimental condition (high intensity, Brain Age) and the control condition (low intensity, Tetris) and for expectation whether the answers changed significantly before and after the intervention.

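### Engagement counts as matched when a difference test at n = 24 is non-significant, and the only concrete engagement–outcome check is run only if a difference appears, so small to moderate imbalances can pass unexamined

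*Protocol article*

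**What the plan says.** All references are to the protocol article.

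- **Secondary Hypotheses.** The third hypothesis is that engagement in the experimental and control conditions, for high versus low intensity and for Brain Age versus Tetris, "are not significantly different from each other".
- **Analysis of Expectation and Engagement.** A linear mixed model with by-participant slopes is used to see "whether any significant differences exist in expectation and engagement between the experimental condition" and the control condition. No margin or confidence-interval criterion is given.
- **Expectation and Engagement.** For the games, "it is expected that no significant difference exists in engagement between Brain and Tetris". The next sentence gives the follow-up: "In case there is a difference, it will be checked whether the performance at the Stroop task" and the fMRI activity correlate with the engagement score. The same section says that differences in enjoyment, motivation, fatigue or satisfaction between conditions might affect cognitive improvement.
- **Stroop Task Analysis.** "Expectations for improvement at the cognitive task also enter as fixed effects into the model". Engagement is not among the listed terms.
- **Blinding; Strength and Limitations.** The first says expectation and engagement will be taken into account in the analysis. The second says they can be checked for correlation with task performance. Neither names a model or a test.
- **Sample Size.** "Calculation of the sample size is not possible because no similar study has been reported to date"; "We also aim to include 24 participants".

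**The concern.** A hypothesis of no significant difference is easier to support the less precise the study is. A non-significant result can mean that engagement was similar, or that 24 people were too few to show that it was not. Without a margin or an interval criterion, the plan cannot tell the two apart.

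The conditional follow-up adds to this. If no difference is found, the one analysis that would show whether engagement tracks Stroop performance or activation is not called for. The article itself regards engagement as a rival explanation, and participants cannot be blinded to the condition. At stake is the attribution of an effect to exercise intensity or to the game: a report could describe the conditions as matched on engagement when the data only failed to show otherwise. The estimates and tests of the primary contrasts are not changed.

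**Working it through.** The article states no power, effect size or SD for engagement, so there is no figure of its own to reproduce.

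**Inputs**
- n = 24 (Sample Size). Each participant rates engagement after all four interventions, twice per game and twice per intensity.
- Two-sided alpha 0.05: assumed, because none is stated for this test.
- dz = true mean difference divided by the SD of the within-person difference: assumed range 0.2 to 0.8.
- A paired t-test stands in for the mixed-model contrast with by-participant slopes. It is an approximation.

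**Chance of missing a true imbalance**

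Power = P(|T| > t₀.₉₇₅,₂₃), where T is noncentral t with 23 df and noncentrality dz × √24. The critical value is 2.069.

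| dz | Noncentrality | Non-significant, n = 24 | Non-significant, n = 20 (assumed loss of 4) |
|---|---|---|---|
| 0.2 | 0.98 | 84% | 86% |
| 0.3 | 1.47 | 71% | 75% |
| 0.4 | 1.96 | 53% | 60% |
| 0.5 | 2.45 | 35% | 44% |
| 0.6 | 2.94 | 20% | 28% |
| 0.8 | 3.92 | 4% | 8% |

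At n = 24, power of 80% needs dz of about 0.60, and 50% needs about 0.42.

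**On the 1–7 scale**

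Take a true imbalance of 0.5 point, and let the SD of the difference range over assumed values. The 95% half-width is 2.069 × SD / √24.

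| SD of difference | dz | Missed | 95% CI half-width |
|---|---|---|---|
| 0.75 | 0.67 | 12% | 0.32 |
| 1.0 | 0.50 | 35% | 0.42 |
| 1.25 | 0.40 | 53% | 0.53 |
| 1.5 | 0.33 | 65% | 0.63 |
| 2.0 | 0.25 | 78% | 0.85 |

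**What an equivalence criterion could show at n = 24**

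With two one-sided 5% tests (90% CI inside ± margin) and a true difference of zero, the chance of showing equivalence is 2%, 22%, 54%, 77% and 91% for margins of 0.3, 0.4, 0.5, 0.6 and 0.7 SD of the difference. A margin of 0.5 SD would need about 36 participants for 80%.

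**The case against.** The strongest reply is that the article does not tie everything to one p-value.

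- **Loose trigger.** The follow-up depends on a difference, not expressly on a significant one. That stands as wording. But significance is the only criterion described, both in the sentence before it and in the analysis section.
- **Games only.** The conditional sentence follows the game comparison, and no such condition is written for exercise intensity. This is correct. But if it covers the games alone, no concrete engagement–outcome check is specified for high versus low intensity at all.
- **General intentions.** Blinding and Strength and Limitations speak of considering engagement without a condition. They leave it unclear whether the check is conditional, but they fix no unconditional analysis.
- **Large imbalances are found.** At 0.8 SD only 4% are missed, and the small imbalances that are missed are the least able to explain an effect. This stands and limits the point to small and moderate imbalances.

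A reader might also infer that a whole safeguard against the lack of blinding switches off. The text does not support that. Concealing the hypothesis is the first safeguard and is untouched. Engagement is only part of the second, and expectation, the other part, enters the Stroop model unconditionally. Nor does any section say that equality will be declared; non-significance is hypothesised and expected. Finally, engagement is rated after each intervention in a randomized crossover. It may be a consequence of the condition, so calling it a baseline confounder would be wrong.

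**Conclusion.** The point holds in limited form. The plan lets a non-significant test with no margin support the engagement hypothesis, and it makes its only concrete engagement–outcome check conditional on a difference.

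At n = 24 the chance of missing a true imbalance runs from 84% at 0.2 SD to 35% at 0.5 SD, then falls to 20% at 0.6 and 4% at 0.8. These figures rest on an assumed two-sided 5% level, an assumed range of standardised differences and a paired-test approximation. The article gives neither the SD nor the imbalance that would matter, so the result is a range. It does not support saying that engagement imbalance in general will be missed.

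The outcome is secondary, but it bears on how the primary effects are explained, so the change should be made.

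**What to change.** 1. Report the High–Low and Brain Age–Tetris engagement differences with confidence intervals.
2. Replace the non-significance hypothesis with equivalence inside a margin on the 1–7 scale, justified and fixed before data lock. Call engagement matched only if the 90% CI lies inside the margin; if it does not, and no difference is shown, report the result as inconclusive. The article offers no basis for a particular margin, so the investigators must supply one.
3. Run the engagement–outcome analysis for Stroop performance and brain activity, for both contrasts, whatever the test shows. Label it a sensitivity analysis and state that it does not replace the unadjusted primary comparison, because engagement is measured after the intervention and may result from it.

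The cost is analysis wording only: the ratings are already collected, and no participants are added. The downside is that equivalence may well not be shown. At a margin of 0.5 SD the chance is about 54% even if the true difference is zero.

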### Stroop Task Analysis

We will use R (R Core Team, 2018) and lme4 (Bates et al., 2015) to perform linear mixed effects analysis of cognitive performance in dependence of physical exercise and video gaming. For reaction time at the Stroop task, we enter physical exercise intensity (high/low), video game (Brain Age/Tetris), week (1, 2, 3, 4), congruency of the Stroop task (congruent/incongruent), age (60–70 years), and gender (male/female) as fixed effects into the model. As random effects, we have intercepts for participants, as well as by-participant random slopes for the effect of physical exercise intensity and video game. Expectations for improvement at the cognitive task also enter as fixed effects into the model and the correlation with other predictors should be checked. For the correct answer count at the Stroop task, we will use the generalized linear mixed-effects model analysis and take the same fixed and random effects as above. Visual inspection of residual plots should be checked to ascertain whether they reveal any marked deviations from homoscedasticity or normality. *P*-values are obtained from likelihood ratio tests of the full model with the effect in question against the model without the effect in question.

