### Randomization

We conduct four interventions per participant and use a Latin square counterbalancing that sums up to four sequences in all (see CONSORT flowchart). First, it would be wasteful for organizational purposes and costs for MRI to cover every possible sequence (24 in total) because it would necessitate 24 separate intervention sessions for each participant. Second, the risk of having a bias because of carry-over effects might be higher when two high-intensity bouts follow each other than with two low-intensity bouts because results demonstrated that biomarker for cognitive improvement (e.g., brain-derived neurotrophic factor, BDNF) might still influence the performance, even after 7 days (Skriver et al., 2014). It is not confirmed, but by separating the two high-intensity bouts from each other, it might decrease this bias. To make it more homogeneous, high-intensity and low-intensity bouts are conducted in an alternating fashion.

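### Likelihood ratio tests with about 24 participants and no small-sample correction are clearly liberal for participant-level terms, including expectation if scored once per person, but only mildly liberal or near nominal for exercise and game

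*Protocol article*

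**What the plan says.** Stroop Task Analysis specifies linear mixed models in lme4 for reaction time. The fixed effects are exercise intensity, game, week, congruency, age and gender. On the random part: "As random effects, we have intercepts for participants, as well as by-participant random slopes for the effect of physical exercise intensity and video game". In addition, "Expectations for improvement at the cognitive task also enter as fixed effects into the model". The count of correct answers gets a generalized linear mixed model with the same terms. P-values are "obtained from likelihood ratio tests of the full model with the effect in question against the model without the effect in question". The reference distribution is not named, and neither is a finite-sample correction.

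On size, the Sample Size section says "We also aim to include 24 participants" and gives no power calculation.

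Expectation and Engagement has expectation rated twice, "after the last session of the familiarization phase and after the last session of the intervention phase". Whether it enters the Stroop model as one score per person or as a score matched to each condition is not stated. Analysis of Expectation and Engagement models the ratings by exercise and game, which suggests condition-specific ratings. That section reuses the Stroop model approach, and Analysis of Physical and Game Performances carries it on to heart rate. Game scores get mixed models of the same kind.

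**The concern.** A likelihood ratio test of a fixed effect compares maximum-likelihood fits and refers the difference to a chi-square distribution, which is a large-sample result. The number of trials (192 per session) does not help a term that is constant within a person. For age, gender and a single expectation score, the information is 24 people less the parameters estimated between people. For exercise and game, with random slopes, it is roughly 24 within-person differences. The chi-square reference ignores these limited degrees of freedom, so P-values can come out too small.

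The secondary hypothesis that expectations correlate with Stroop performance is at stake. The Blinding section offers expectation and engagement, alongside keeping participants unaware of the hypothesis, as its response to the lack of blinding. A false positive here would colour how any exercise or game effect is read.

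**Working it through.** The article states no type I error for the Stroop tests, so there is no figure of its own to reproduce.

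**Inputs.** n = 24 (Sample Size). Random intercept and two random slopes (Stroop Task Analysis). Four-sequence Latin square with intensities alternating (Randomization). Assumed: chi-square reference, two-sided 0.05, week as a factor, the coding of expectation, and the variance components.

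**Analytic size.** For a one-parameter contrast tested against between-participant variation with df residual degrees of freedom, LRT = n × ln(1 + t²/df). The test rejects when this exceeds 3.841, that is when t² > df × (exp(3.841/n) − 1). For n = 24 the bracket is exp(0.1601) − 1 = 0.1736.

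| n | df | Corresponds to | Rejects at \|t\| above | Correct 5% cut-off | True size |
|---|---|---|---|---|---|
| 24 | 23 | exercise or game contrast | 1.998 | 2.069 | 5.8% |
| 24 | 20 | age, gender, one expectation score (24 − 1 − 3) | 1.863 | 2.086 | 7.7% |
| 24 | 19 | as above with two expectation scores | 1.816 | 2.093 | 8.5% |
| 20 | 19 | exercise or game contrast | 2.006 | 2.093 | 5.9% |
| 20 | 16 | one expectation score | 1.841 | 2.120 | 8.4% |
| 20 | 15 | two expectation scores | 1.782 | 2.131 | 9.5% |

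The n = 20 rows illustrate losses. Eligibility Criteria drops people below 80% correct from the analysis, and the article does not say how many this might be.

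**Simulation.** The formula simplifies the model, so the full model was simulated under the null: correlated random intercept and slopes, ML fits, chi-square tests, n = 24, 4,000 data sets per scenario (Monte Carlo standard error about 0.35 to 0.5 points).

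| Term | True size, slopes varying | True size, slope variance zero |
|---|---|---|
| Exercise | 5.4–6.4% | 3.8% |
| Game | 5.1–5.6% | 4.3% |
| Congruency | 5.3–5.7% (5.3% with trial-level data) | 6.5% |
| Week (3 df) | 6.1–8.0% | 5.7% |
| Age | 8.9–10.5% | 8.5% |
| Gender | 9.5–11.3% | 9.2% |
| Expectation, one coefficient, scored per person | 8.5–11.0% | 9.8% |
| Expectation, one coefficient, condition-specific | 8.9–9.9% | not run |

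A joint two-parameter test of expectation gave 10.6 to 13.1%.

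A second, smaller simulation (800 data sets per scenario, standard error about 0.7 to 1.1 points) agreed on direction. With small slope variance, exercise was 3.4–3.5% and game 4.3–5.6%; with larger slope variance both were 5.0–6.9%. Congruency was 4.4–5.3% throughout. Condition-matched expectation ratings gave 5.3% and 6.0% with small slopes, and 7.6% and 9.4% with larger ones. Across the two simulations, condition-specific ratings therefore span about 5 to 10%.

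No simulation of the full model with an F-test was run. In the analytic setting, an F reference with the right df has size 5% by construction.

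**The case against.** The strongest objection is that the primary hypotheses are hardly touched. For exercise and game the excess is about one point or less on most figures, and its sign depends on how much the slopes vary, which nobody knows yet. This stands. A reader might infer that every fixed-effect test is anti-conservative; the simulations do not support that, since game and congruency are near nominal and exercise and game can fall below 5%.

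A reader might also infer that a stated 5% level is missed. The article gives P < 0.05 only for the fMRI clusters, so 0.05 for the Stroop tests is an assumption.

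Third, the figure for expectation depends on a coding that the article does not fix. This stands, and it is why a range is given for each coding.

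Fourth, one might call the expectation test the plan's main defence against unblinded participation. The Blinding section lists unawareness of the hypothesis first, then expectation and engagement together. A liberal expectation test would also over-flag expectancy, which urges caution and does not manufacture an intervention effect. Both points are fair and limit the consequence.

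Finally, the chi-square reference is inferred, and a bootstrap reference would also be a likelihood ratio test. That is true, but chi-square is the ordinary reading for lme4 models, and the article itself chooses the test, so this is not merely detail left to an analysis plan.

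**Conclusion.** The point holds in limited form. Followed in the ordinary way, the plan tests age, gender and a per-person expectation score at about 8 to 11% when 5% is intended. If expectation is condition-specific, the rate is about 5 to 10%. Exercise runs at about 6% if its effect varies between people. Game and congruency are close to nominal, and exercise and game may be near 4% if slope variance is negligible.

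The result rests on the chi-square reference, a two-sided 0.05 level, about 24 analysed participants and assumed variance components. It matters for the secondary expectation hypothesis and does not materially threaten the primary behavioural contrasts.

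**What to change.** Replace the sentence on P-values. Fit the linear mixed models by REML and test fixed effects with Kenward-Roger or Satterthwaite F-tests, which are available for lme4 fits. For the correct-answer generalized model, keep the likelihood ratio statistic but take its reference distribution from a parametric bootstrap. Apply the same rule to the models for expectation, engagement, heart rate and game scores. In the same edit, state the significance level for the Stroop tests and whether expectation enters as one score per person or one per condition, because its degrees of freedom depend on that.

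The cost is a short change of wording, an add-on R package and somewhat more computation. P-values for participant-level terms will become larger. For exercise and game the change should be small, and it need not be upward if slope variance is near zero. No design change or new data are needed.
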